### Intervention

Patients in the five CHCs randomised to the intervention group who were screened as non-adherent to their antihypertensive drugs will receive a tailored pharmacist-led intervention during two sessions (at baseline and at a 1-month follow-up) in addition to usual care. Both will be regular outpatient visits, when patients collect their medication. The intervention will be low cost, aligned with the current CHC workflow and will not require a substantial change to the current system. Before the study started, the intervention steps and materials were piloted in two pharmacies and optimised in an iterative process.

#### Intervention at baseline (first session)

Before dispensing antihypertensive drugs during the first session, the pharmacist will discuss patient-specific barrier(s) for medication adherence based on their responses to the MARS questionnaire and three additional questions, which are derived from the Brief Medication Questionnaire^21^ (figure 2). The intervention strategy will then be tailored to the identified adherence problems. Based on the current literature,^22–24^ we defined four non-adherence problems that can be addressed by the community pharmacists, that is, (1) forgetfulness, (2) lack of knowledge, (3) lack of motivation and/or (4) other drug-related problems. Of note, patients might need a combined intervention strategy to address all experienced problems. The four non-adherence problems and recommended intervention strategies are specified in table 1. The session will end with involving patients in goal setting and writing the agreed goal at the top of the personalised leaflet. Pharmacists will remind patients to take his/her leaflet to the next visit.

**Table 1 T1:** Non-adherence problems and recommended intervention strategies

Non-adherence problems	Intervention strategies
1. Forgetfulness	Strategies to cope with forgetfulness include reminders, habit-based strategies and/or involvement of family members, and improving knowledge on what to do when a dose is forgotten.^23^ The use of a reminder tool or pill boxes will be encouraged and a reminder app can be implemented if the patient owns a mobile phone. The habit-based strategy will be delivered through a personalised leaflet, which is tailored to the patient’s daily routine (online supplementary appendix C). Patients will be asked to identify the appropriate place and time to take their medication, and an activity they conduct every day that could serve as a prompt or cue to take their medication.^31^ Patients will be asked to write coping plans to formulate their own ‘if–then’ plans for the daily doses of their antihypertensive drug(s).^31^ Moreover, patients will be asked to choose a family member to become their treatment supporter and to write down the name of a family member on the personalised leaflet. This individual will be asked to support the patient to take antihypertensive drugs. Pharmacists will keep a copy of the leaflet and remind patients to take his/her personalised leaflet to the next visit.
2. Lack of knowledge	Patient counselling by the pharmacist to cope with lack of knowledge may focus on educating the patient about the purpose of the medication, when and how to take the medication, the need for long-term use, the importance of medication adherence and how to deal with possible side effects. To explore which education is needed, the patient will be asked whether they know why and how to take their medication. The teach-back method will be used, where the patient is asked to explain to the pharmacist what he/she has understood after receiving the education.^32^
3. Lack of motivation	Counselling to cope with a lack of motivation will focus on exploring and discussing the patients’ concerns and necessity beliefs. This method is called motivational interviewing.^33^ This is done by asking the first question about whether the medication bothers the patient. Follow-up on this question can focus on reducing any concerns or low necessity beliefs (eg, when patients are bothered by the medication because they think the medication is not needed or are afraid of side effects).
4. Other drug-related problems	Counselling to address other drug-related problems will focus on exploring other problems underlying non-adherence, for example, experiencing side effects, costs, polypharmacy, difficulty to refill antihypertensive drugs in time or medication intake problems, and offering solutions/alternatives when possible.

**Figure 2 F2:**
[figure not shown]
Flowchart of a targeted and tailored intervention at baseline visit (T0). Type of intervention: 1=reminders, habit-based strategies and/or involvement of family member; 2=counselling to increase knowledge (teach-back method); 3=counselling to increase motivation; 4=explore/address other drug-related problems. MARS: Medication Adherence Report Scale.

#### Interventions at follow-up (second session)

The follow-up session will be conducted 1 month after the baseline session, when patients refill their medication at the next regular outpatient visit (figure 3). The purpose of the follow-up session is (1) to evaluate the short-term effect of the intervention and discuss the patients’ implementation of and experiences with the offered information and recommendations, and (2) to address non-adherence problems that were not yet addressed during the first session. Where needed, the pharmacist, together with the patient, can make changes to the coping plan and discuss additional interventions. The session will end with involving patients in goal setting and writing the agreed goal at the top of the personalised leaflet.

**Figure 3 F3:**
[figure not shown]
Flowchart of a targeted and tailored intervention at the 1-month follow-up visit (T1). Type of intervention: 2=counselling to increase knowledge (teach-back method); 3=counselling to increase motivation; 4=explore/address other drug related problems. MARS: Medication Adherence Report Scale.

#### Pharmacist training

As the quality of the intervention will depend on the competences and skills of the pharmacist, treatment integrity will be enhanced by an obligatory communication training focusing on how to elicit and classify barriers to adherence, the teach-back method and motivational interviewing, and by providing support material as part of the intervention (figure 4).

**Figure 4 F4:**
[figure not shown]
Proposed adherence intervention wheel as supportive material for pharmacists in the intervention group.

Pharmacists and patients participating in this study will be compensated with a modest souvenir at the end of the study for their time and effort.

### Control group

Patients in the five CHCs randomised to the control group will receive pharmacist counselling based on the Indonesian guideline of pharmacy practice (PMK No.74/2016).^19^ At each visit, they can receive information about the quantity and dose of the dispensed drugs, when and how to use and store the drugs, side effects and how to deal with them, the importance of medication adherence, and confirming if the patient understands how to take medications correctly. Patients in the control group who were screened as non-adherent to their antihypertensive drugs by the research assistant at baseline will complete the assessments at the same time points as those in the intervention group.

### Outcomes

#### Primary outcome

The primary outcome is the difference between the intervention and the control group in the change in the MARS score from baseline (T0) to a 3-month follow-up (T2). The Indonesian version of the MARS showed to be valid (correlation value of each question to the total score >0.396) and reliable (Cronbach α coefficient of 0.803).^25^ Patients will indicate how often each statement applied to them in the last 3 months on a 5-point Likert scale ranging from always (score 1) to never (score 5). Items are summed to obtain a total score ranging from 5 to 25 (Horne R. The Medication Adherence Report Scale (MARS): a new measurement tool for eliciting patients’ reports of non-adherence).

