### Sample size calculation

The sample size calculation is based on the formula for cluster randomised trials, powered on the primary outcome.^29^ We want to be able to detect a difference between the intervention and control group in the change in adherence score of at least 2.5 points with an expected SD of 3.8 points and assuming an intracluster correlation coefficient within CHCs of 0.014, as calculated based on the previous work from our group (manuscript in preparation). A sample size of 41 non-adherent patients in each study arm (intervention and control group) would allow for 80% power to detect this difference using a two-sided test at the 5% level of significance. Assuming non-adherence rates of 50%^30^ and a dropout rate of 20%, we will recruit at least 100 patients in each group, giving a total of 200 patients from 10 CHCs (20 per CHC) that need to complete the MARS screening. Recruiting at least 20 patients per CHC is feasible as the average number of diabetes patients with hypertension visiting a CHC is around 30 patients per month.

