### Planned statistical analysis

Data analysis will be performed based on the intention-to-treat principle. Descriptive statistics will be used to summarise the baseline characteristics. To control for the effects of cluster randomisation, group changes will be compared (individual CHCs will be treated as a random effect) using multivariate mixed linear and non-linear regression for normally and non-normally distributed data, respectively. Point estimates estimated from cluster-adjusted models will be reported with 95% confidence intervals . We will conduct subgroup analysis using data stratification on diabetes complications and the number of concomitant medications to assess the effect of the intervention. All tests will be two-tailed and p*<*0.05 will be considered statistically significant. All statistical analyses will be carried out using SPSS software (V.25).

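### The primary comparison is set on MARS change without naming baseline MARS as a covariate, which can cost precision and leaves chance baseline imbalance in the estimate

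*Protocol article*

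**What the plan says.** Three sections of the Protocol article put the primary comparison on change from baseline.

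- **Primary outcome**: "the difference between the intervention and the control group in the change in the MARS score from baseline (T0) to a 3-month follow-up (T2").
- **Sample size calculation**: the trial is powered for a between-arm difference in "the change in adherence score of at least 2.5 points", "with an expected SD of 3.8 points", "assuming an intracluster correlation coefficient within CHCs of 0.014". It does not say whether 3.8 is the SD of the change or of a single score.
- **Planned statistical analysis**: "group changes will be compared (individual CHCs will be treated as a random effect) using multivariate mixed linear and non-linear regression". CHC is the only model term named. The word multivariate implies further covariates, but none is listed.

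Two design features bear on the point. Under Participants, entry requires MARS below 20 on a scale that runs from 5 to 25. Under Randomisation and blinding, Intervention and Control group, ten CHCs are allocated 1:1, five to each arm.

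**The concern.** A change score subtracts the whole baseline value, so it fixes the slope of the month-3 score (T2) on the baseline score (T0) at 1. If the true slope differs from 1, a baseline difference between the arms passes into the treatment estimate, multiplied by (slope − 1).

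Here the change is likely to depend on the starting score. A patient entering at 19 can gain at most 6 points, and one entering at 10 can gain 15. Patients are also selected on the variable that is later subtracted. With five CHCs per arm, the arms may differ at baseline by chance.

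At stake are precision in a small cluster trial and the reading of the result if the arms start apart. Baseline MARS is collected on every enrolled patient, so the information to deal with both is already there.

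**Working it through.** **Inputs from the Protocol article.** Difference 2.5, SD 3.8, ICC 0.014, 41 per arm, 80% power at two-sided 5%, five CHCs per arm, 20 patients screened per CHC with 50% non-adherent.

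**Inputs not given, so assumed.** T0–T2 correlation r from 0.3 to 0.7; SD ratio k = SD(T0)/SD(T2) from 0.5 to 1; baseline SD from 2 to 3 points; slope of T2 on T0 of 0.5, varied from 0.3 to 0.7; ICC of baseline MARS equal to 0.014.

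**1. The plan's own figure.** The article states "A sample size of 41 non-adherent patients in each study arm" for "80% power to detect this difference using a two-sided test at the 5% level of significance".

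- Unclustered n per arm = 2 × (3.8 × (1.960 + 0.842) / 2.5)² = 36.27.
- With 20 × 50% = 10 non-adherent patients per CHC, the design effect is 1 + 9 × 0.014 = 1.126.
- 36.27 × 1.126 = 40.84, so 41. Power at 41 is 80.2% by the normal approximation.

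The figure reproduces. If 3.8 is the SD of the change, an unadjusted change analysis meets its target on the plan's own method.

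**2. Chance imbalance.** With 41 patients over five CHCs, the mean cluster size is 8.2 and the design effect is 1 + 7.2 × 0.014 = 1.1008.

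- SE of the baseline difference = SD × √(2/41 × 1.1008) = SD × 0.2317, which is 0.46 for SD 2 and 0.70 for SD 3.
- 95% limits: 1.96 × SE = ±0.91 to ±1.36 points.
- Shift in the change estimate = (slope − 1) × imbalance. At slope 0.5 its size is 0.45 to 0.68 points, in the direction opposite to the imbalance. Divided by 2.5, that is 18% to 27% of the target.
- At slope 0.3 the shift is 0.64 to 0.95 points; at slope 0.7 it is 0.27 to 0.41.

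Using the design effect of 1.126 instead gives 0.46 to 0.69 points at slope 0.5 (18% to 28%).

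**3. Precision.** The variance of the baseline-adjusted estimate relative to the change-score estimate is (1 − r²) / (1 + k² − 2rk). It never exceeds 1, because the denominator minus the numerator is (r − k)². It reduces to (1 + r)/2 when k = 1.

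| k | r = 0.3 | r = 0.5 | r = 0.7 |
|---|---|---|---|
| 1 | 0.650 | 0.750 | 0.850 |
| 0.85 | 0.751 | 0.860 | 0.958 |
| 0.7 | 0.850 | 0.949 | 1.000 |
| 0.5 | 0.958 | 1.000 | 0.927 |

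The saving is 35% down to 15% with equal SDs. It is between 0% and 25% if the entry limit narrows the baseline SD to 0.5 to 0.85 of the T2 SD. It is zero when r = k.

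**4. What the most favourable case would mean.** If 3.8 is the SD of the change and k = 1, the residual SD falls to 3.06, 3.29 or 3.50 for r = 0.3, 0.5 or 0.7. The plan's formula then needs 27, 31 or 35 per arm instead of 41.

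**5. Equivalence of the two models.** Write change = a + b·arm + c·T0. Adding T0 to both sides gives T2 = a + b·arm + (c + 1)·T0. The treatment coefficient b is the same, and the CHC random effect does not alter this. The outcome definition can therefore stay on change.

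**The case against.** The strongest objection is that the plan does not say what a reader might infer, namely that raw changes will be compared in place of a baseline adjustment. The outcome section defines an outcome, not a model. The analysis section announces a multivariate mixed model and lists no covariates. By step 5, a change outcome is compatible with full adjustment. The covariate list may also sit in a full protocol or analysis plan that is not shown. This stands: the text neither provides for adjustment nor rules it out. What remains is that the article sets out the outcome, the contrast and the clustering term, and that wording permits an unadjusted change analysis.

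A reader might also infer a large gain in power. With 40 per arm, 8 per CHC, SD of change 3.8 and a t reference with 8 degrees of freedom, power is 69%, and with equal SDs it rises to 86%, 81% or 76% for r = 0.3, 0.5 or 0.7. The documents do not support that as the effect of adjustment.

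- The 69% comes mainly from the 8-df reference, not from using change scores; the plan's own method gives 80.2% at 41 per arm.
- It relies on reading 3.8 as the SD of the change.
- The rise needs k = 1, yet the entry limit at MARS below 20 is a reason to expect a narrower baseline SD. With k of 0.5 to 0.85 the variance saving may be nil.

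Nor can it be said outright that a change score over-corrects for baseline. The slope is r/k, and over-correction needs a slope below 1. With k = 0.5 and r = 0.7 the slope is 1.4, and the change score under-corrects.

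Finally, randomisation makes the change estimate unbiased on average. The imbalance argument is conditional on the allocation that occurs.

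**Conclusion.** The point holds as a matter of efficiency and of bias conditional on imbalance. It does not invalidate the analysis or the sample size. The primary comparison is framed on change, baseline MARS is not named as a covariate, and naming it is never less precise in large samples.

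The imbalance effect is about 0.45 to 0.7 points at the 95% limits of chance, 18% to 27% of the 2.5-point target, given a baseline SD of 2 to 3, a slope of 0.5 and an ICC of 0.014. The variance saving lies anywhere from none to about a third. The article gives neither the T0–T2 correlation nor the SD ratio, so it cannot be narrowed further. The change is worth making because it costs almost nothing, not because a particular gain in power can be promised.

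**What to change.** In Planned statistical analysis, state that the primary analysis is a linear mixed model of T2 MARS (or, equivalently, of MARS change) on arm and patient-level baseline MARS, with CHC as a random effect, and that the adjusted mean difference in points is reported with its 95% confidence interval. Use the same form for systolic pressure, diastolic pressure and the BMQ scores, each adjusted for its own baseline.

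The outcome definition, the 2.5-point target and data collection do not change. The cost is one sentence and one covariate that is already collected. While editing, it would help to state in Sample size calculation whether the SD of 3.8 refers to the change or to a single score.

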#### Secondary outcomes

##### Blood pressure level

Within and between patient changes in blood pressure (BP) level (systolic blood pressure and diastolic blood pressure) will be assessed. BP measurements will be performed by a nurse who is blinded to the group assignment at baseline (T0), 1-month (T1) and 3-month (T2) follow-up.

##### Medication beliefs

Within patient, changes on beliefs about the medication will be assessed using the Beliefs about Medicines Questionnaire (BMQ)-specific at baseline (T0) and a 3-month follow-up (T2). The Indonesian version of the BMQ-specific showed to be valid (correlation value of each question to the total score >0.530) and reliable (Cronbach α coefficient of 0.835 and 0.811 for necessity and concerns beliefs, respectively). The BMQ-specific contains five items about necessity beliefs (eg, ‘My health at present depends on my blood pressure-lowering medicines’), five items about concern beliefs (eg, ‘I sometimes worry about becoming too dependent on my blood pressure-lowering medicines’) and one item about side effects (eg, ‘My blood pressure-lowering medicines gives me unpleasant side effects’). All items have a 5-point Likert scale ranging from strongly disagree to strongly agree with an overall range from 5 (low necessity, low concern) to 25 (high necessity, high concern). A necessity–concern differential score will be calculated by subtracting the scores of the concerns scale from the necessity scale (range −20 to 20). A positive differential score indicates stronger beliefs in the necessity, whereas a negative score indicates stronger concerns.^26^ The additional item about side effects will be analysed separately due to its known role in non-adherence.^22 27^

##### Process evaluation

We will conduct a process evaluation to assess other parts of the RE-AIM framework. In short, the RE-AIM framework has been developed to evaluate public health interventions assessing five dimensions (reach, efficacy, adoption, implementation and maintenance) at multiple levels (eg, individual or organisation).^18^
*Reach* will be assessed by measuring the participation rates and representativeness of patients who participate in this study. In case a patient refuses or discontinues to participate in this study, the patient’s age, gender and BP-lowering drugs the patient uses will be recorded by research assistants. This information is used to calculate the participation rate and assess differences between responders and non-responders. To determine representativeness, the patients’ demographics will be compared with census demographics in Bandung City, Indonesia. *Adoption* will be evaluated by assessing the proportion and representativeness of CHCs who participate in this study, and exploring pharmacists’ and patients’ satisfaction with and willingness to use various parts of the intervention. *Implementation* will be evaluated by determining whether the intervention was delivered as intended and exploring pharmacists’ and patients’ suggestions for future implementation. *Maintenance* will be assessed by determining whether the intervention can be maintained and the willingness of pharmacists and payers to continue the intervention as part of routine clinical practice. We will use focus group discussions at a 1-month (T1) follow-up and an evaluation survey (based on a previously used survey)^28^ at a 3-month follow-up (T2) to explore pharmacists’ and patients’ adoption, implementation and willingness to maintain the intervention, respectively.

### Baseline participant and CHC characteristics

Participants’ baseline characteristics, including sociodemographic and clinical-related factors, will be obtained. Sociodemographic factors are self-reported and include age at the completion of the questionnaire, gender, highest level of education completed (no formal education/elementary high school, junior high school, senior high school or university) and type of health insurance. Type of health insurance will be classified as those whose insurance premium was paid by the government (BPJS-PBI), those whose insurance premium was paid by the patients themselves (BPJS-Non PBI) or those without health insurance. Clinical-related factors include time since diagnosis of diabetes and hypertension (years), diabetes complication(s) that developed after the diagnosis of diabetes, and types and number of concomitant medications. The following diabetes complications will be considered: cardiovascular conditions, cerebrovascular conditions, nephropathy, retinopathy, neuropathy and diabetic foot problems. Clinical-related factors will be collected by research assistants using a predefined data collection form. Furthermore, organisational information of each CHC (number of medical doctors, pharmacists, nurses and average number of patients with diabetes with and without hypertension visits per month) and pharmacist characteristics (age, gender and working experience in community pharmacy (years)) will be collected by research assistants using a predefined data collection form.

### Treatment fidelity

Treatment fidelity will be addressed by providing a checklist of items that pharmacists need to do at each patient visit and a counselling protocol for the intervention group (online supplementary appendix D). Pharmacists will be asked to complete the checklist after each visit with a study participant. The completed checklists will be collected on a weekly basis and used to calculate an overall fidelity score. Minor feedback suggestions from the PI to pharmacists will be made if needed.

### Sample size calculation

The sample size calculation is based on the formula for cluster randomised trials, powered on the primary outcome.^29^ We want to be able to detect a difference between the intervention and control group in the change in adherence score of at least 2.5 points with an expected SD of 3.8 points and assuming an intracluster correlation coefficient within CHCs of 0.014, as calculated based on the previous work from our group (manuscript in preparation). A sample size of 41 non-adherent patients in each study arm (intervention and control group) would allow for 80% power to detect this difference using a two-sided test at the 5% level of significance. Assuming non-adherence rates of 50%^30^ and a dropout rate of 20%, we will recruit at least 100 patients in each group, giving a total of 200 patients from 10 CHCs (20 per CHC) that need to complete the MARS screening. Recruiting at least 20 patients per CHC is feasible as the average number of diabetes patients with hypertension visiting a CHC is around 30 patients per month.

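### The stated 80% power for a 2.5-point difference overlooks that only five health centres per arm estimate the between-centre variance; power is about 70% on 8 df and about 76% at most

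*Protocol article*

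**What the plan says.** The sample size section of the protocol article powers the trial on the primary outcome, the between-arm difference in MARS change. The target difference is 2.5 points and the SD is taken as 3.8. Clustering enters through one value, the authors "assuming an intracluster correlation coefficient within CHCs of 0.014". For a two-sided 5% test, the section concludes: "A sample size of 41 non-adherent patients in each study arm (intervention and control group) would allow for 80% power to detect this difference". It then takes 50% non-adherence and 20% dropout and sets a target of at least 100 screened patients per arm, 20 at each of 10 CHCs.

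The Randomisation, Intervention and Control group sections allocate CHCs 1:1, five to each arm. Under Planned statistical analysis, "group changes will be compared (individual CHCs will be treated as a random effect") in a mixed regression model. The sample size section refers only to a published formula for cluster randomised trials. It does not say how, or whether, the small number of clusters was allowed for.

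**The concern.** Arm varies only between CHCs, so the arm contrast is judged against the variation among CHC means within arm. With five CHCs per arm, that variation is estimated from few units: 2 × (5 − 1) = 8 degrees of freedom, with a two-sided 5% critical value of 2.306 rather than 1.960. A design effect raises the variance for the ICC but treats the result as known. If the stated 80% was reached that way, it is too high for an analysis that estimates the CHC variance from ten centres.

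At stake is the chance of missing a true 2.5-point effect on the primary outcome. The stated chance is 20%; on 8 degrees of freedom it is about 30%. A reader weighing a non-significant result against the stated power would credit the trial with more sensitivity than it has.

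**Working it through.** **Inputs.** From the sample size section: difference 2.5, SD 3.8, ICC 0.014, two-sided 5%, 41 per arm. From the Intervention and Control group sections: five CHCs per arm. From the recruitment chain: 100 screened × 50% non-adherent × 80% retained = 40 analysable per arm, or 8 per CHC.

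**1. Reproducing the plan's figure.**
- Individually randomised: n = 2 × (1.960 + 0.842)² × 3.8² / 2.5² = 36.27, rounded up to 37 per arm.
- Design effect 1 + (m − 1) × 0.014: 1.098 for m = 8, and 1.126 for m = 10.
- 37 × 1.098 = 40.6, or 36.27 × 1.126 = 40.8. Both round up to 41.
- Power at 41 per arm (m = 8.2, design effect 1.1008): 81.0% with a normal reference, 80.1% with a t reference on 80 patient-level degrees of freedom.

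The stated 41 and 80% therefore reproduce by several routes. None of them allows for there being only ten CHCs.

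**2. Power on cluster-level degrees of freedom.** The standard error is 3.8 × √(2 × design effect / n), the noncentrality is 2.5 / SE, and the reference is a noncentral t on 8 df.

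| Analysable per arm | Design effect | SE | Noncentrality | Normal power | Power, 8 df |
|---|---|---|---|---|---|
| 41 (m = 8.2) | 1.1008 | 0.881 | 2.839 | 81.0% | 70.2% |
| 41 (m = 10 in the design effect) | 1.126 | 0.891 | 2.807 | 80.2% | 69.2% |
| 40 (m = 8) | 1.098 | 0.890 | 2.808 | 80.2% | 69.2% |

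The difference detectable with 80% power on 8 df is 2.82 points at 41 per arm (m = 8.2) and 2.85 at 40.

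**3. Simulation, to cover other reference distributions.** The set-up was 10 CHCs × 8 patients, ICC 0.014, SD 3.8, with the CHC variance estimate not allowed below zero, and at least 40,000 trials per setting.

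| Reference for the arm effect | Power at 2.5 points | Type I error |
|---|---|---|
| Cluster-level t test, 8 df | about 69% | about 5% |
| Mixed model, Satterthwaite-type df | 68–69% | about 3.7% |
| Mixed model, residual df | about 75% | about 4.5% |
| Mixed model, normal reference | about 76% | about 4.8% |

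The CHC variance is estimated as zero in about 48% of trials and otherwise lies above zero. The estimated standard error therefore tends to be too large, which is why even the normal reference falls short of the 80.2% in step 2.

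**4. Sensitivity to the ICC.** Larger values are assumptions and do not come from the article. At 40 per arm on 8 df: ICC 0.03 gives 65%, and 0.05 gives 60%. At ICC 0, 41 per arm on 8 df gives 74.2%, so most of the loss comes from the number of CHCs and little from the ICC itself.

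**The case against.** The strongest reply is that the article fixes no degrees-of-freedom method, so 69–70% is the power of one possible test. That stands. A reader might infer that the planned test has 69–70% power, but the documents support only a range of about 68–76%. The choice of method may properly sit in an analysis plan that is not shown, so its absence is not held against the article. A later plan could not, however, make the stated 80% correct at 40 to 41 per arm.

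A second reply is that at the article's own ICC the less conservative references are valid. This also stands: their type I error is about 4.5–4.8%. They exceed 5% only at larger ICCs; the same simulation at an assumed ICC of 0.05 gives 5.8% with residual df and 6.2% with a normal reference. Eight degrees of freedom are thus a safeguard in case the ICC exceeds 0.014, and the stated inputs do not by themselves require them.

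A reader might also infer that the sponsor used a normal approximation with 10 patients per CHC. Several routes lead to 41, and the cited formula is not at hand, so the documents do not show which was used. It is likewise tempting to say that baseline adjustment would recover most of the loss. The article gives no baseline-to-follow-up correlation, so no size can be put on that.

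Finally, recruitment is set as a minimum, and more patients would help. If all 50 enrolled per arm completed, power would be 77.5% on 8 df and, in simulation, about 84% with a normal reference. But the 80% claim is attached to 41 per arm, and the article's own dropout assumption leaves 40.

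**Conclusion.** The concern holds in this form: the stated power is too high for the stated numbers. At 40 to 41 analysable patients per arm in five CHCs each, power for 2.5 points is about 69–70% on cluster-level degrees of freedom and about 75–76% with residual df or a normal reference. The shortfall is roughly 4 to 12 percentage points, depending on the method. On 8 df, 80% power corresponds to about 2.8 points.

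These figures assume equal CHC sizes, SD 3.8 applying to the change score, ICC 0.014 and no precision gain from covariates. Unequal CHC sizes would lower power; covariate adjustment might raise it. The sample size formula is not misapplied on its own terms. The fault is that its result is presented as the power of an analysis that must estimate CHC variance from ten centres.

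**What to change.** In the sample size section, replace the 80% statement with: about 70% power for 2.5 points (up to about 76% depending on the degrees-of-freedom method), or 80% power for about 2.8 points, given 10 CHCs, 40 to 41 analysable patients per arm, SD 3.8 and ICC 0.014. If a range of ICCs is shown, label it as an assumption: about 65% at 0.03 and about 60% at 0.05, with 40 per arm and 8 df.

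State also that the restated power refers to a small-sample reference for the arm effect: Satterthwaite or Kenward-Roger degrees of freedom, or a cluster-level t test on 8 df. This guards against an inflated type I error if the ICC exceeds 0.014.

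The cost is wording only. No patients or CHCs are added and the outcome and intervention are unchanged; the stated power becomes less favourable.
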